## Abstract

**Background:**

Alcohol use disorder (AUD) is highly prevalent and commonly co-occurs with other psychiatric disorders among Veterans. Provisional evidence supports the use of Approach Avoidance Training (AAT) - a form of computer-delivered cognitive bias modification designed to target implicit approach bias for alcohol-related cues - as an adjunctive program to treat AUD. However, the extent to which AAT is effective for improving AUD recovery outcomes in outpatient Veteran samples and those with psychiatric comorbidities has been understudied to date. Here we describe a double-blind randomized controlled trial of AAT versus a comparison condition (Sham) being conducted in Veterans with comorbid psychiatric conditions completing outpatient standard care.

**Methods:**

One hundred thirty-six Veterans currently receiving outpatient treatment for AUD will be recruited for this randomized controlled trial with parallel group assignment. Participants will be randomized to either 6 weeks of AAT (n = 68) or Sham (n = 68) training in conjunction with usual care. Assessments will occur at baseline and 6 weeks, 3 months, and 6 months post-baseline. Primary outcome variables will include functional consequences of drinking. Secondary outcome variables will include alcohol consumption, and behavioral indicators of alcohol approach bias. A subset of participants (n = 51) will also complete functional magnetic resonance imaging (fMRI) to assess neural response during an alcohol approach bias assessment.

**Discussion:**

This study is the first randomized controlled trial of AAT administered as an adjunctive treatment to standard care in Veterans with AUD and comorbid psychiatric disorders. Additionally, behavioral and neuroimaging data will be used to determine the extent to which AAT targets approach bias for alcohol cues. If effective, AAT may be a promising low-cost adjunctive treatment option for individuals with AUD.

**Registry name:**

AAT for Alcohol Use Disorder in Veterans.

**Trial registration:**

ClinicalTrials.gov: NCT05372029; Date of Registration: 5/9/2022.

**Supplementary Information:**

The online version contains supplementary material available at 10.1186/s12888-023-04961-z.

## Background

Alcohol use disorder (AUD) is the most common substance use disorder among Veterans [1, 2] and results in substantial functional impairment and adverse outcomes spanning poor health, under or unemployment, legal consequences, financial stressors, and social disruption [3–6]. Psychiatric comorbidity is frequent among Veterans with AUD, with estimates of co-occurring psychiatric disorders exceeding 30% [7, 8], which often further exacerbates functional problems and is associated with increased relapse rate and earlier relapse [9]. Psychosocial (e.g., Cognitive Behavioral Therapy [CBT]) and pharmacotherapies are considered frontline treatments for both AUD and associated psychiatric disorders, yet relatively high relapse rates point to a continued need to identify novel clinical targets to improve outcomes [10–16].

Dual process models of AUD propose that problematic use arises from an imbalance of two conflicting, partially independent sets of processes that could be targeted clinically [17–20]. The first is relatively diminished functioning of top-down, reflexive control systems [19], associated with self-regulation and goal-directed behavior, supported by frontoparietal neural circuits (e.g., dorsolateral and ventrolateral prefrontal cortex (dLPFC; vPFC) and anterior cingulate (ACC)). The second is an over activation of bottom-up, impulse-based responding rooted in mesocorticolimbic circuitry (e.g., medial prefrontal cortex (mPFC), striatum) [18]. The latter process is driven in part by a high attribution of incentive salience to alcohol related cues, whereby over the course of repetitive alcohol use individuals develop an excessive appetitive orientation toward alcohol-related stimuli (i.e., “wanting”) [21, 22]. This increased incentive salience may instigate, increase, or enhance craving and alcohol seeking behaviors [23]. Standard psychotherapy approaches typically engage explicit, top-down regulatory strategies in the service of reducing alcohol use, (e.g., Cognitive-Behavioral Therapy for substance use disorders [24]). Devising interventions that more directly engage bottom-up, automatic processes holds promise for improving clinical efficacy of available interventions targeting both components thought to drive addiction [25, 26].

Cognitive bias modification is an intervention technique designed to adjust maladaptive cognitive-affective biases. In these interventions, participants repeatedly perform one or more tasks designed to reverse or oppose maladaptive biases, typically via computer-guided exercises targeting the automatic processes thought to drive symptoms. One particularly promising form of cognitive bias modification for AUD is Approach Avoidance Training (AAT). AAT for AUD targets approach bias for alcohol-related cues (i.e., automatic action tendencies to approach alcohol-related cues based on implicit appetitive motivational responses). AAT is based on the premise that positively evaluated stimuli typically elicit automatic motor approach behaviors (i.e., approach action tendencies), whereas negative stimuli trigger avoidance [27]. A common task to assess approach and avoidance behavioral responding displays valenced stimuli and asks the participant to pull a joystick (arm flexion; approach) or push it away (arm extension; avoidance) in response to the color of the image border or orientation, with faster approach versus avoidance movements seen for positively evaluated stimuli [28, 29]. Individuals with AUD commonly exhibit a bias demonstrated by faster response to pull versus push alcohol cues [19]. This basic assessment paradigm was adapted to create an AAT *intervention* by establishing a contingency between stimulus valence and required responses to encourage repeated approach or avoidance of cues [30]. In AAT for AUD, participants repeatedly practice behavioral disengagement from alcohol cues (i.e., pushing away), with the goal of changing implicit approach-oriented biases for alcohol related cues.

Growing evidence supports the use of AAT as an adjunctive program with treatment for substance use disorders including AUD [31–36]. A recent randomized clinical trial found that four sessions of AAT increased the likelihood of abstinence by 17% following discharge of inpatient withdrawal facilities [33]; additionally, AAT administered during inpatient treatment has been shown to improve abstinence rates at 1-year follow-up versus control and sham conditions by 8.4% [35]. Facets of approach and avoidance dysfunction have been observed in a variety of psychiatric conditions, suggesting that the presence of comorbid conditions with AUD could impact AAT treatment effects [37–39]. To our knowledge, the efficacy of AAT for AUD has not been evaluated among outpatient participants specifically recruited for presence of comorbid conditions, nor in Veterans. Given the prevalence of AUD (estimated at over 10% [6]) and comorbid conditions in Veterans with AUD, there is a need for further therapeutic development in this population. Finally, the broader impact of AAT on clinical outcomes beyond abstinence remains understudied, which is critical given that abstinence alone is insufficient to capture functional recovery [40–43].

Questions also remain about the underlying neural mechanisms of AAT. Preliminary data suggests that that AAT may shift neural responses in approach system regions during alcohol cue processing. Wiers and colleagues (2015) found that a cognitive bias modification training (AAT) relative to a control condition (Sham) administered to individuals seeking treatment for alcohol use disorder, was associated with a greater reduction in alcohol cue-elicited activation in the bilateral amygdala, which correlated with decreases in craving [44]. A subset of those patients completed an additional scan task assessing behavioral approach tendencies toward alcohol cues (i.e., performed Approach Avoidance Assessment during fMRI), which revealed a significant interaction effect of time by group, where participants who completed AAT showed reductions in the mPFC in the contrast of interest ([alcohol pull > alcohol push] >[soft drink pull > soft drink push]) from pre- to post-training relative to those who completed Sham training [45]. However, to date there have been relatively few studies that have explored neural mechanisms of AAT treatment.

To address these current knowledge gaps, the present study will conduct a randomized controlled trial of AAT versus a comparison condition in Veterans being treated for AUD plus comorbid psychiatric conditions in outpatient Veterans Affairs (VA) care. The trial adopts a mechanistic approach by including comprehensive measurement of outcome across clinical, functional, and neurobiological assessments.

## Methods

### Aims

The primary aim is to determine the efficacy of AAT training compared to Sham training as an adjunctive treatment in Veterans with AUD undergoing standard care. We intend to evaluate if repeatedly practicing avoidance of alcohol cues through AAT cognitive bias modification can improve functional recovery outcomes and reduce hazardous drinking.

The secondary aim is to determine if AAT reduces approach bias for alcohol cues, as measured with behavioral and functional neuroimaging data.

### Trial design

The proposed study is a randomized, double-blind, parallel-group controlled trial. This protocol has been formulated in accordance with the Consolidated Standards of Reporting Trials (CONSORT) 2010 Statement guidelines [46].

### Study setting

Data collection will take place at the VA San Diego Healthcare system. Participants will be recruited through the San Diego VA outpatient addictions treatment program. Upon initiation of treatment, patients who meet study eligibility criteria will be offered the opportunity to participate in the clinical trial in addition to standard care.

### Sample size

Sample size determinations for the functional outcomes were made with a series of power calculations conducted using RMASS power calculation software for longitudinal mixed models. Parameters entered into the calculation included an effect size of d = 0.6 [32], 4 time points, attrition ranges between 20 and 25% based on rates in a prior VA-based clinical trial with a similar sample [47], and α = 0.05. Under the most conservative retention rate, we will need to enroll 136 participants to achieve 80% power. Sample size determinations for imaging outcomes were made using R:WebPower software for analysis of variance for a treatment group x time interaction term. Parameters entered into the calculation included an effect size of d = 0.80, 2 time points, and attrition as above with α = 0.05. We will need a sample of n = 51 to achieve 80% power to detect a treatment group x time effect on the regions encompassed within our a priori mask.

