### Participants and study design

We plan to evaluate 176 Veterans between the ages of 18–65 with the goal of randomizing 136 participants. Participants will be randomized at the individual level to AAT or Sham. Participants will participate in a functional magnetic resonance imaging (fMRI) in addition to the AAT training and behavioral study assessments, unless they are unable to safely complete scanning procedures (see Fig. 1).

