#### Neuroimaging group level analysis

Linear mixed effects models will be used to evaluate whether BOLD activation changes differentially over time and group (AAT training versus Sham) for the primary contrast of interest. The primary fMRI outcome is the difference in BOLD response to the alcohol pull-push > neutral pull-push contrast, which is a continuous outcome variable reflecting differential activation to the task conditions at each voxel of the brain. We will use a threshold adjustment based on Monte-Carlo simulations (AFNI’s 3dClustSim) to ensure Type I error is controlled when interpreting significant brain clusters that are active. The simulations will be generated in a single mask of three a priori anatomical regions of interest (ROIs) previously identified as impacted by AAT in the context of an RCT to treat AUD, including the bilateral amygdala, mPFC, and striatum. The linear mixed effects model conducted in AFNI 3dLME will include condition (AAT vs. Sham) as a between-subject factor and time (baseline, post-training) as the within-subjects factor, with participant included as a random factor. The hypothesis that AAT recipients, relative to Sham recipients, will demonstrate reduced approach bias would be supported by an interaction of condition by time on BOLD activation in the primary contrast of interest.

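### The fMRI sample of 51 contains no attrition allowance, although attrition is listed as an input; the plan must say whether 51 is counted before or after loss

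*Protocol article*

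**What the plan says.** All references are to the protocol article.

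- **Sample size, method:** "Sample size determinations for imaging outcomes were made using R:WebPower software for analysis of variance for a treatment group x time interaction term".
- **Sample size, inputs:** "Parameters entered into the calculation included an effect size of d = 0.80, 2 time points, and attrition as above with α = 0.05". The attrition referred to is the 20 to 25% given for the main outcome earlier in the same paragraph.
- **Sample size, result:** "We will need a sample of n = 51 to achieve 80% power to detect a treatment group x time effect", for the regions in the a priori mask.
- **Abstract, Methods:** "A subset of participants (n = 51) will also complete functional magnetic resonance imaging (fMRI").
- **Participants and study design:** participants have fMRI in addition to training and behavioural assessment, "unless they are unable to safely complete scanning procedures". No upper limit on scans is stated there.
- **Neuroimaging group level analysis:** the mixed model will "include condition (AAT vs. Sham) as a between-subject factor and time (baseline, post-training) as the within-subjects factor". It is fitted voxel by voxel, with a simulation-based cluster threshold inside a single mask of three regions.

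For the main outcome, the Sample size section gives 136 as the number to enrol under the worst assumed retention.

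**The concern.** A reader who sees attrition among the inputs and 51 as the result will take 51 as already inflated for loss, as 136 is for the main outcome. The Abstract invites the same reading, because it gives 51 alongside the randomised totals of 136 and 68 per arm. If 51 was in fact computed without loss, a team that stops after 51 baseline scans will finish with fewer evaluable pairs than the calculation needs, and scans not done at baseline cannot be recovered later.

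The fMRI contrast carries part of the secondary aim, namely whether training changes approach bias at the neural level. A null result would be reported against a stated 80% power. If the true figure were 67 to 70%, the chance of missing an effect of the assumed size would be 30 to 33% instead of 20%.

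**Working it through.** **Inputs from the Sample size section:** d = 0.80; 2 time points; alpha = 0.05; target power 80%; loss 20 to 25%. Two arms at 1:1 come from the Allocation section. Sidedness is not stated, but a 1-df interaction F test is equivalent to a two-sided test.

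**Formula.** With two arms and two times, the group-by-time interaction equals a two-sample comparison of change scores:
- f = d/2 = 0.40
- noncentrality λ = f² × N = 0.16 × N
- degrees of freedom 1 and N − 2
- power = P(noncentral F > 95th percentile of the central F)

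This takes d as standardised on the change score, and it is the reading that reproduces the plan's figure.

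**Step 1. Reproduce 51.** At N = 51, λ = 0.16 × 51 = 8.16, the critical F(1, 49) is 4.038 and power is 0.7996. Solving for exactly 80% gives N = 51.05. The stated 51 is therefore reproduced with zero loss.

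**Step 2. If 51 are scanned at baseline.**

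| Loss | Pairs left | λ | Power | d detectable at 80% |
|---|---|---|---|---|
| 0% | 51 | 8.16 | 79.96% | 0.80 |
| 20% | 51 × 0.80 = 40.8, taken as 41 | 6.56 | 70.5% | 0.90 |
| 25% | 51 × 0.75 = 38.25, taken as 38 | 6.08 | 67.0% | 0.93 |

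**Step 3. If 51 must have both scans.** Baseline scans needed are 51/0.80 = 63.75, so 64, and 51/0.75 = 68. Insisting on at least 80.0% means 52 pairs (power 80.7%), hence 52/0.80 = 65 and 52/0.75 = 69.3, so 70.

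**Step 4. Can 51 be reached with loss included?**
- A one-sided 5% test needs 40.06 pairs: 50.1 scanned at 20% loss, 53.4 at 25%.
- If d is on the raw SD with a pre-post correlation of 0.6, 41.3 pairs are needed: 51.6 scanned at 20% loss, 55.0 at 25%.

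Each route needs an input the plan does not state, and each comes near 51 only at the milder loss rate.

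**Step 5. Optional gain from baseline adjustment.** The correlation ρ between the two scans is my assumption; the article gives none. The change-score variance is 2σ²(1 − ρ) and the baseline-adjusted variance is σ²(1 − ρ²), so their ratio is 2/(1 + ρ). The effective d is 0.80 × √(2/(1 + ρ)). Power at 38 pairs, against 67.0% for the interaction test:

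| Assumed ρ | Variance ratio | Variance saved, (1 − ρ)/2 | Effective d | Power |
|---|---|---|---|---|
| 0.3 | 1.54 | 35% | 0.99 | 84.5% |
| 0.5 | 1.33 | 25% | 0.92 | 79.1% |
| 0.6 | 1.25 | 20% | 0.89 | 76.5% |

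**The case against.** The strongest defence is that 51 means completers. The Sample size section speaks of enrolling 136 but only of a sample of 51, and the Abstract says the subset will complete fMRI. The numbers also fit: 51/0.75 = 68, exactly half of 136. Scanning depends on MRI safety, with no cap, so 64 to 68 baseline scans could well accrue. Fig. 1, whose caption covers planned enrolment and attrition, may give the count, but it is not shown in the text available. This defence stands as a possible reading, and under it the 80% is sound. It does not remove the defect in the wording, because the visible text still lists attrition as an input to a calculation whose result contains none.

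A reader might therefore infer that the imaging aim is simply underpowered. The documents do not support that as a fact, because nothing says that 51 is the number entering the scanner. Nor does scanning everyone who is eligible contradict 51: one is a procedure and the other can be a power target. They conflict only if 51 is a cap, which the article does not say.

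Two further objections are fair. Powering one summary test for a voxelwise analysis is a simplification that limits what the 80% describes, not an arithmetic error. And the condition-by-time interaction is a valid test under randomisation, so baseline adjustment is an improvement, not a correction.

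**Conclusion.** The point holds as an error of statement. Under the inputs the plan gives, 51 is the zero-attrition sample size (79.96% power), so the claim that attrition was entered does not agree with the result.

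The consequence is conditional:
- **51 scanned at baseline:** power is about 70% at 20% loss and 67% at 25%, with detectable d of 0.90 and 0.93.
- **51 with both scans:** power is 80%, and the missing number is the 64 to 68 to be scanned at baseline.

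Both rest on d being standardised on the change score, a two-sided 5% test, near-equal arms, and imaging loss matching the plan's 20 to 25%. Both describe a single mask-level test; power of the cluster-corrected voxelwise analysis is not given by this calculation. Severity is moderate: this is a secondary outcome in a subset, and the primary DrInC analysis is unaffected.

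**What to change.** 1. **Correct the Sample size section and the Abstract.** State that 51 is the number needed with both scans, that about 64 (20% loss) to 68 (25% loss) baseline scans are therefore required, and that scanning under the rule in Participants and study design does not stop at 51 baseline scans. If 51 really is the number entering, restate the power as 67 to 70%. Align Fig. 1 with whichever is chosen.
2. **State the scope of the figure.** Add that the power refers to one test on a mask-level summary, not to the cluster-corrected voxelwise map.

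Both are wording changes. The restatement itself needs no extra scans; keeping 80% power does require that 64 to 68 people are scanned at baseline.

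3. **Optional.** Analyse the post-training contrast with the baseline contrast as covariate, or keep the mixed model and constrain the arms' baseline means to be equal. The plan already adjusts DrInC for baseline. The cost is a changed model specification, set before the data are analysed. The gain at 38 completers, from 67% to about 77 to 85%, depends on the assumed correlation of 0.6 to 0.3 and should be reported as such.

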### Participants and study design

We plan to evaluate 176 Veterans between the ages of 18–65 with the goal of randomizing 136 participants. Participants will be randomized at the individual level to AAT or Sham. Participants will participate in a functional magnetic resonance imaging (fMRI) in addition to the AAT training and behavioral study assessments, unless they are unable to safely complete scanning procedures (see Fig. 1).

**Fig. 1 Figa:**
[figure not shown]
Flow Chart of Study Design and Planned participant enrollment and attrition *Note.* AAT = Approach avoidance training

### Eligibility criteria

Participants must be Veterans between 18 and 65 years of age (inclusive of all sexes); have a primary diagnosis of AUD (i.e., meet *Diagnostic and Statistical Manual of Mental Disorders, Fifth Edition* (DSM-5) criteria for AUD); have no more than 90 days abstinence from alcohol prior to study participation; and must have 4-week stability if taking psychotropic medications at the time of enrollment. Participants will be excluded if they have a lifetime history of psychotic or bipolar disorder; neurodegenerative or neurodevelopmental disorders; history of moderate or severe traumatic brain injury or other known neurological conditions; sensory deficits that would preclude completing behavioral tasks; suicidal or homicidal ideation within the past month necessitating urgent higher level care; concurrent individual psychotherapy or other treatment outside of standard clinical programming; conditions unsafe for completing MRI scanning for those completing the scanning component only (e.g., non-scan safe metal in body).

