### Outcomes

#### AUD-related disability (primary)

The Drinker Inventory of Consequences (DrInC) assesses alcohol-related adverse functional consequences across physical (e.g., harmed physical health), interpersonal (e.g., loss of relationships), role responsibilities (e.g., missed work), psychological (e.g., loss of hobbies), and impulse control-related problems (e.g., legal problems); the first administration establishes lifetime consequences (DrINC-2 L) and a modified version of the DrInC-2R will be used to assess past 30-day consequences, and subsequent administrations assesses past 30-day consequences [48].

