#### Recent alcohol and other substance use (secondary)

During each study visit, alcohol consumption will be quantified using the Time Line Follow-Back (TLFB). During this interview, participants are asked to report the number of days alcohol and other drugs were consumed as well as alcohol type,quantity, and beverage size using a calendar method. Percentage days heavy drinking ( > ≡ 4/5 drinks per single occasion for women/men) (PDHD) will be calculated as the TLFB outcome [49]. The TLFB will capture 90 days preceding the baseline appointment. At all subsequent visits, the TLFB will cover the time between interviews.

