## Outcomes and statistical methods

### Primary and secondary clinical outcomes

To evaluate whether AAT significantly improves clinical outcomes relative to Sham, a mixed effects model repeated measures (MMRM) model will be used. The dependent variable in the MMRM model is change from baseline in AUD-related disability (DrInC) at each post-baseline visit (post visit, 3 and 6 mo. follow-up). Predictors in the model will include treatment condition (AAT, Sham), visit (immediately post-training, 3 and 6 mo.), condition by visit interaction term, and baseline DrInC. The primary end point is the post-training visit. The same analytic approach will be applied to the secondary outcome (PDHD). We will model the distribution of percent days heavy drinking to ensure appropriate analysis. All subjects randomized will be included in the intent-to-treat analysis. Depending on the type of missing data, the appropriate statistical approach (e.g., multiple imputation) will be determined. Sensitivity analyses will be used to explore the impact of missing data.

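### Entry allows up to 90 days of abstinence but the baseline DrInC looks back 30 days, so baseline DrInC, the primary model's only patient-level covariate, mixes severity with recency of last drink

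*Protocol article*

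**What the plan says.** All references are to the Protocol article.

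- **Eligibility criteria:** participants must "have no more than 90 days abstinence from alcohol prior to study participation". No minimum of recent drinking and no minimum baseline DrInC score is stated.
- **AUD-related disability (primary):** the first administration has a lifetime form, and "a modified version of the DrInC-2R will be used to assess past 30-day consequences"; "subsequent administrations assesses past 30-day consequences".
- **Recent alcohol and other substance use (secondary):** "The TLFB will capture 90 days preceding the baseline appointment".
- **Primary and secondary clinical outcomes:** "The dependent variable in the MMRM model is change from baseline in AUD-related disability (DrInC) at each post-baseline visit". The predictors are condition, visit, "condition by visit interaction term, and baseline DrInC". "The primary end point is the post-training visit".

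The entry rule and the secondary TLFB thus share a 90-day horizon, while the primary scale uses 30 days. The article does not say which form supplies the baseline for the change score. The 30-day form is the only one comparable with follow-up, so it is taken as the baseline here.

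**The concern.** A patient whose last drink was 31 to 90 days before baseline satisfies the entry rule but has no drinking inside the baseline DrInC window. Two things follow.

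1. The baseline score is likely to be at or near the minimum, so there is little or no room for it to fall. The primary aim speaks of improving functional recovery. In these patients the arms can separate mainly through relapse in one arm and averted relapse in the other.
2. The baseline score carries two messages at once: how severe the alcohol problem is, and how recently the patient drank. Someone with severe disorder who stopped five weeks ago gets a score similar to someone with few consequences. The model has no other patient-level term to tell them apart.

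At stake are the precision of the primary contrast and a clear reading of what the mean change represents.

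**Working it through.** **Step 1. The windows side by side.**

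| Item | Look-back |
|---|---|
| Abstinence allowed at entry | up to 90 days |
| TLFB at baseline | 90 days |
| DrInC at baseline (repeated form) | 30 days |
| DrInC at later visits | 30 days |

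The uncovered group is last drink 31 to 90 days before baseline: eligible, visible in the TLFB, with no drinking in the DrInC window.

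**Step 2. The plan's sample size.** The article gives d = 0.6, four time points, 20 to 25% attrition, alpha 0.05 and 136 participants for 80% power. The simple two-mean formula gives 2 × (1.960 + 0.842)² / 0.6² = 43.6, so 44 per arm, 88 in total and 118 after 25% attrition. A four-visit group-by-time model with 25% dropout gives 134 (compound symmetry, correlation 0.3) or 136 (AR(1), correlation 0.7), but 60 to 194 over correlations of 0.3 to 0.7. The correlation is not stated, so 136 is attainable and can be neither confirmed nor called wrong. Nothing below depends on it.

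**Step 3. What the covariate loses.** Assumptions, none of them in the article: severity S is normal with SD 1 and mean m (in SDs above zero); its correlation with follow-up is r = 0.5, so it explains 25% of variance; a share f is abstinent for more than 30 days, independently of severity, and scores 0 at baseline; those patients score δ SD lower at follow-up.

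- Variance of follow-up: V = 1 + δ²f(1 − f)
- R² with the 30-day baseline alone: (1 − f)(r + δfm)² / [(1 + fm²)V]
- R² with a recent-drinking indicator added: [(1 − f)r² + δ²f(1 − f)] / V

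Example with f = 0.3, δ = 0, m = 2.25: 0.7 × 0.25 / (1 + 0.3 × 5.0625) = 0.175 / 2.519 = 7.0%. With the indicator: 0.7 × 0.25 = 17.5%. Residual variance ratio: 0.825 / 0.930 = 0.89.

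| f | δ | R², baseline alone (m = 1 / 1.5 / 2.25 / 3) | R² with indicator | Fall in residual variance |
|---|---|---|---|---|
| 10% | 0 | 20.5 / 18.4 / 14.9 / 11.8% | 22.5% | 3 to 12% |
| 10% | 0.5 | 24.2 / 23.8 / 21.9 / 19.6% | 24.2% | 0 to 6% |
| 30% | 0 | 13.5 / 10.4 / 7.0 / 4.7% | 17.5% | 5 to 13% |
| 30% | 0.5 | 21.6 / 20.9 / 18.5 / 16.2% | 21.6% | 0 to 6% |

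A simulation with 400,000 draws agrees with each cell to within 0.3 percentage points. The indicator raised or held explained variance in every case. The result depends strongly on m, the mean severity in SD units.

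**Step 4. Power, as illustration only.** If a share f showed no arm difference at all and the SD were unchanged, d would be 0.6(1 − f). Anchored to the stated 80%, power is Φ(2.802(1 − f) − 1.960): 71%, 61% and 50% at f = 10%, 20% and 30%. A two-sample t-test with 51 per arm (68 less 25%) starts at 85% and gives 77%, 67% and 56%. If these patients showed half the effect, d = 0.6(1 − f/2) and the t-test gives 81%, 77% and 72%. The first case is the worst one. The documents supply neither f nor the effect in this group.

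**The case against.** **The floor is not absolute.** A reader might infer that these patients start at the floor and cannot improve. The article does not support that. Its examples of consequences, such as harmed health, lost relationships and legal problems, can outlast the last drink by more than 30 days, and no scores for abstinent patients are given. This objection stands: the wording must be at or near the floor.

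**Relapse prevention is information.** With baseline as covariate, the treatment estimate is the same whether change or follow-up score is modelled, so a patient at the floor still contributes through relapse or its prevention. The evidence cited in the Background concerns abstinence after inpatient care, which is relapse prevention. This stands too, and makes the no-effect case in Step 4 a worst case.

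**Dilution of d = 0.6 is not shown.** A reader might conclude that the trial is underpowered. The population behind the cited effect size is not visible. If it included similarly abstinent patients, 0.6 already reflects them.

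**The group may be small.** Enrolment accompanies treatment initiation, and training starts in the first week of outpatient treatment. This may limit the number but excludes nobody, and the 90-day allowance admits such patients explicitly.

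**A lifetime DrInC is collected.** It measures severity independently of recent abstinence. It is not named in the model, however, and as baseline for a change score it would not be comparable with a 30-day follow-up.

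**An extra covariate is analysis-plan detail.** This would hold if the article were silent. It is not: it lists the predictors of the primary model, and the point concerns how that list interacts with the entry rule and the scale's window.

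**Conclusion.** The mismatch holds on the article's own text: 90 days at entry, 30 days for the primary scale, and baseline DrInC as the only patient-level covariate. Patients last drinking 31 to 90 days before baseline enter with a score that probably lies at or near the floor and confounds severity with recency.

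The consequence is lost precision and a harder reading of mean change. Randomisation protects the comparison, so there is no bias. Under the Step 3 assumptions, a recent-drinking indicator lowers residual variance by 3 to 13% if abstinence is unrelated to outcome and by 0 to 6% if abstinent patients score 0.5 SD lower at follow-up. These ranges rest on an assumed share (10 or 30%), an assumed 25% of variance explained by severity, and an assumed mean severity of 1 to 3 SD. The power figures show what could happen at worst and do not establish that the planned power is lost.

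The change is worth making because it costs almost nothing and did no harm in any scenario examined.

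**What to change.** 1. Add one prespecified covariate to the primary MMRM, taken from the baseline TLFB: any drinking in the 30 days before baseline (yes/no), or days since last drink. Choose one form and fix it before unblinding. State at the same place that the 30-day DrInC form supplies the baseline. Cost: one degree of freedom and a sentence of analysis wording; no new data.
2. Keep the 30-day DrInC window at all visits. Widening only the baseline window to match the entry rule would make the stated change score compare unequal periods and leave anyone already enrolled with a different baseline.
3. Optional: report the primary contrast in patients with drinking in the 30 days before baseline as a supportive analysis. It uses the same data, and its cost is a smaller sample, so it should not replace the analysis of all randomised participants.
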